## Abstract

**Background:**

Interventions such as advance care planning (ACP), technology, or access to euthanasia may increase the sense of control over the end of life. In people with advanced dementia, the loss of cognitive and physical function limits the ability to control care. To date, little is known about the acceptability of these interventions from the perspective of persons with dementia and others involved. This study will examine the cross-cultural acceptability, and factors associated with acceptability, of four end-of-life interventions in dementia which contain an element of striving for control. Also, we report on the development and pilot testing of animation video vignettes that explain the interventions in a standardized manner.

**Methods:**

Cross-sectional mixed-methods vignette study. We assess acceptability of two ACP approaches, technology use at the end of life and euthanasia in persons with dementia, their family caregivers and physicians in six countries (Netherlands, Japan, Israel, USA, Germany, Switzerland). We aim to include 80 participants per country, 50 physicians, 15 persons with dementia, and 15 family caregivers. After viewing each animation video, participants are interviewed about acceptability of the intervention. We will examine differences in acceptability between group and country and explore other potentially associated factors including variables indicating life view, personality, view on dementia and demographics. In the pilot study, participants commented on the understandability and clarity of the vignettes and instruments. Based on their feedback, the scripts of the animation videos were clarified, simplified and adapted to being less slanted in a specific direction.

**Discussion:**

In the pilot study, the persons with dementia, their family caregivers and other older adults found the adapted animation videos and instruments understandable, acceptable, feasible, and not burdensome. The CONT-END acceptability study will provide insight into cross-cultural acceptability of interventions in dementia care from the perspective of important stakeholders. This can help to better align interventions with preferences. The study will also result in a more fundamental understanding as to how and when having control at the end of life in dementia is perceived as beneficial or perhaps harmful.

**Trial registration:**

The CONT-END acceptability study was originally registered at the Netherlands Trial Register (NL7985) at 31 August, 2019, and can be found on the International Clinical Trials Registry Platform.

## Background

The central theme in what is regarded as a good death in western countries, is control [1]. Attempts to exert control at the end of life are emotionally charged and controversial. This is obvious from controversies around interventions such as euthanasia and assisted dying. In dementia, retaining control is inherently difficult due to cognitive decline. Issues with end-of-life care may be complicated by impaired decisional capacity and decreased ability to express preferences or complaints such as pain.

Palliative care assumes that anticipating and preparing for the end of life is beneficial [2, 3] and advance care planning (ACP) for the end of life is part of it. ACP involves discussing and documenting the desired direction of the patient’s care with patients and their family caregivers, thereby providing some control over current and future care. Positive effects of ACP on end-of-life care with dementia have been reported [4, 5]. However, dementia decreases the ability to imagine future situations, and coping (well) with dementia implies that preferences can change substantially [6]. For example, people’s prior perceptions of whether they will be enjoying life with moderate or severe dementia can be inaccurate. Also, the course of the disease cannot be predicted accurately [3]. If the perceived control turns out to be unrealistic or does not match desired levels or negatively impact relationships, perceived control can cause more distress than the perception of no control at all [7]. So, ACP in dementia is not without its challenges.

Despite many barriers to initiating ACP with persons with dementia [8, 9], some work indicates that ACP is acceptable in dementia care [5]. However, much less is known about whether persons living with dementia prefer a specific approach to ACP. For example, people might prefer to detail specific future treatments or they might simply prefer to discuss their goals and values regarding future care. In this study, we focus on the acceptability of two ACP approaches when applied to dementia care [10, 11]. The first ACP approach focuses on advance treatment orders in detail and thus capitalises on being in control. The second ACP approach focuses on setting global goals of care and coping with disease.

While ACP may provide some control over future decisions, there are interventions at the end of life that may provide more sense of control. At one extreme, people choosing assisted dying or euthanasia can dictate the time, place and manner of their death. Since 2002, Dutch law has regulated euthanasia with the Termination of Life on Request and Assisted Suicide Act, which legalized the ending of life by physicians at the request of patients suffering unbearably without hope of relief. The same year, Belgium adopted a law on euthanasia that is largely similar to the Dutch law [12]. Canada has legalized suicide assistance or euthanasia by physicians or nurse practitioners in 2016 [13, 14]. Euthanasia can also be legally practiced in Luxembourg, Colombia, Spain, some states of Australia, and in New Zealand. Physician-assisted suicide (PAS), not euthanasia, is legal in Switzerland, in a handful of US states and, more recently, in Austria. In Germany, the Federal Constitutional Court has overturned the prohibition of ‘business-like’ suicide assistance in the penal code in 2020, making it legally available again to commit suicide with the voluntary help of third parties [15].

The debate on legalizing euthanasia and PAS is controversial. Complete consensus seems to be unachievable due to incompatible normative frameworks that clash [16]. Differences in attitudes towards ending life upon request have been associated with differences in countries’ economic, religious and health-related factors [17]. Based on a 48-country survey study, there appears a rough West-East division in euthanasia acceptance among the European public, with relatively high acceptance in Western European countries compared to low to moderate acceptance in the other countries [18]. Public support for euthanasia and PAS in the US ranges between 47 and 69%, with higher public support for euthanasia than PAS [19]. The Netherlands is a country among the top in Europe with regard to public euthanasia acceptance [18, 19]. A total of 60% of the Dutch public agree euthanasia is acceptable for people with advanced dementia. Interestingly, far fewer physicians consider performing euthanasia in this population acceptable, only 8–24% [20]. In Japan, views about the acceptance of euthanasia, in general, are vary greatly depending on the study population [21–24]. So far, however, research about the acceptability of euthanasia across all these nations has primarily focussed euthanasia in general and on family caregivers, ‘the public’ or physicians. Much less is known about how acceptable people with dementia find euthanasia.

Technological advances in medicine imply patients, family caregivers and physicians need to make increasingly difficult end-of-life decisions. The growing use of technology in healthcare raises new questions such as, if, when and how the use of technological aids can affect the dying process. For example, distressing symptoms are common at the end of life in persons with dementia [25]. Patients’ self-report of discomfort is considered the “gold standard” [26]. However, in the terminal phase, patients may not be able to self-report their symptoms. This implies a loss of control in expressing their discomfort and needs and having to rely on others to observe discomfort. Automated pain and discomfort detection by continuous monitoring of facial expressions, activity and vital signs is being developed and may also be available for the dying [27, 28]. Nurses may then respond to technical signals from a distance rather than using bedside observations alone. As such devices are developed and implemented in care, it is important to understand the views of persons with dementia, their family caregivers and physicians about the use of monitoring technology (e.g. medical devices that can recognize distress) at the end of life.

To optimize care for persons with dementia, physicians need to understand differing attitudes toward end-of-life care and which factors to consider when discussing end-of-life decisions with persons with dementia and families from diverse backgrounds. Acceptability of interventions that increase control may vary by life view and personality. Control may be helpful in some cases. Early research in psychology for example, found that beliefs about having (some) control promote adjustment with life-threatening disease [29, 30]. With uncontrollable disease, however, acceptance in the sense of ability to tolerate the nature of the disease can help redirect personal goals, change personality in a positive way and strengthen relationships [31]. Control or goal engagement is the opposite, in a way, to acceptance or letting go. However, it is more complicated than that. For example with aging, people adjust goals to what is feasible which buffers their sense of control [32]. Moreover, both control and acceptance can improve wellbeing. Also, manageability, together with comprehensibility and meaningfulness allows people to better cope with adversities [33, 34]. More generally, there is a need for research to address the complexities and underlying question of how and when attempts at retaining control over the end of life is beneficial and acceptable for whom, and to explain individual and possible cross-national differences.

In this study, the perspectives of persons with dementia, their family caregivers, and physicians in six countries (Netherlands, Japan, Israel, US, Germany, Switzerland) will provide insight into the cross-cultural acceptability in dementia care of two ACP approaches, the use of monitoring technology at the end of life, and euthanasia.

### Objectives

The primary objective is to investigate the acceptability of the four interventions (i.e., whether the participants would want the interventions at the end of life: persons with dementia for themselves, family caregivers for their relative, and whether physicians would use it at request). The secondary objectives include examining differences in acceptability between groups and countries, and to explore associations between acceptability and other participant characteristics (e.g., demographics, variables indicating life view such as religion, and personality variables such as coping style). We use open-ended questions in the interviews to examine qualitatively possible ambiguity regarding being in control through the interventions and in what situations and why the participants feel the interventions are or are not acceptable.

## Methods

The Attempts to CONTrol the END of life in people with dementia (CONT-END) acceptability study was originally registered at the Netherlands Trial Register (NL7985) at 31 August, 2019, and can be found on the International Clinical Trials Registry Platform. The study has a cross-sectional mixed-methods design with participants evaluating intervention vignettes and completing a survey. The vignette scripts, storyboards and early versions of the animation videos were pilot-tested between March and June 2020. Data for the CONT-END acceptability study are collected in the Netherlands, US, Germany, Switzerland, Japan and Israel. The study will be conducted according to the principles of the Declaration of Helsinki (Fortaleza, Brazil, October 2013).

An independent Ethics Advisory Committee was installed as a requirement of the funder, which included representatives from most participating countries in the study, including one member of the Alzheimer Association, to ensure that ethical issues that may arise are also treated in a manner that is sensitive to the international differences. The main remit is to review documents and to monitor the project’s progress from an ethics point of view. The Ethics Advisory Committee members do not receive compensation for their time and are not otherwise involved in the study.

### Selection of countries

The interventions offer different levels of control and their acceptability may vary between countries, groups and individuals. The countries in this study were selected based on literature about large differences in end-of-life care, access to means to exercise control and norms regarding autonomy, technology and sanctity of life [35–45].

First, there may be differences in acceptability of the ACP interventions between countries. This is based on literature about patient autonomy versus relational autonomy or influence of the family or professional caregiver on end-of-life decision making, and legalisation of assisted suicide and not euthanasia in Switzerland and US states (e.g., [35]). Physicians in Germany have much decision-making authority [45]. Physicians in the Netherland are more “paternalistic” than in the US regarding end-of-life treatment decisions in dementia [46]. However, in the Netherlands there is also a focus on self-management with health even proposedly defined as “the ability to adapt and to self-manage” [47].

Second, inhabitants of technology-minded countries with aggressive life-prolonging treatment and infrequent withholding of treatment at the end of life to allow a “natural course” might be most in favour for using technology in the dying. By contrast, in the Netherlands, less aggressive care is common in dementia at the end of life (e.g. low antibiotic use and invasive rehydration) [48–50], as is withholding life-prolonging treatment if it does not improve quality of life [51]. Rates of withholding treatment may be comparable in Switzerland [43, 52]. Further, three countries are known for technological advances: Israel, Japan and the US. These countries are also known for high rates of feeding tubes in people with advanced dementia [36, 38, 39].

Third, a number of publications [36, 44] have shown that sanctity of life is an important value in end-of-life decision making in Israel and Japan. Germany is distinct within Europe for low acceptance of euthanasia [45]. In the Netherlands, on the other hand, euthanasia is legal when fulfilling certain criteria, and the country was at the forefront of euthanasia legislation [41, 45].

### Hypotheses

For the acceptability of the interventions per group, we expect that the ACP intervention with detailed advance treatment orders will be most often acceptable and euthanasia least often acceptable in physicians. No hypotheses on acceptability rated by persons with dementia compared to the other groups are formulated because not enough is known about their views on this matter to formulate specific hypotheses. With regard to acceptability by country, we hypothesize that the ACP intervention with detailed advance treatment orders will be most often acceptable in countries where patients have high autonomy in decision making about medical procedures and care, and where people may feel they need a defence against medical overtreatment, while sanctity of life is not necessarily a dominant principle (in particular, the US). Technology for symptom monitoring when unable to self-report, such as use of cameras in the dying phase, is expected to be most often acceptable in technology-minded countries (Japan, Israel and US). Euthanasia may be most often acceptable in countries that have euthanasia or PAS regulation already in place for a while (in particular the Netherlands and Switzerland) and the least acceptable in countries where ending life is highly controversial (Germany, Israel and Japan).

For the explorative analyses, we expect demographics, variables indicating life view such as religion, view on dementia, attitudes regarding life-prolonging treatment and death and dying, and variables indicating personality such as coping strategy to be associated with acceptability of the interventions. These aspects of life view and personality are selected because they may relate to control. In explaining diversity in acceptability of ACP, individual differences may be more important than differences between countries and respondent groups (hypothesized based on a study in physicians in the UK and the Netherlands; [53]), with those tending to planning as a coping strategy more likely to find the interventions acceptable. Contrary, it could be that people with higher death anxiety are less likely to find the interventions acceptable, as it has been related to fewer preparations for death in people with advanced cancer [54, 55].

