### Sample size calculation

The number of participants is determined by the primary objective of the trial (acceptability). We will use logistic regression analyses and before the COVID-pandemic, we aimed at a total of 6 (countries) x 3 groups) x 50 = 900 respondents for sufficient power according to the 10 events per variable rule of thumb, for a minimum acceptability or non-acceptability rate of 10%. Therefore, with percentages of 10% and up, power would suffice to assess differences between 6 countries and 3 respondent groups. Testing of associations with other characteristics, i.e. life view and demographic and personality characteristics, is exploratory. Also see paragraph ‘Adjustments to protocol’.

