For the adjusted protocol a new power calculation was performed. We will use logistic regression analyses and expect that collecting physician data (n = 50) in a total of 6 (countries) results in 300 physician respondents. Power depends strongly on the type of intervention as this has varied, so far in data collected in the Netherlands, the US and Japan, from acceptable for almost all (advance care planning interventions) to acceptable for closely around half. According to the 10 events per variable rule of thumb, for 7 variables, with 300 respondents, 70 events suffice for acceptability in ratios close to half of respondents, but would not suffice for interventions that are (not) acceptable for the large majority of the respondents. However, examining associations with acceptability is less relevant for interventions which are endorsed or rejected by the great majority.

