### Data analyses

Descriptive statistics will be used to present the acceptability of the four interventions. The internal consistency of the scales will be calculated using Cronbach’s alpha. Descriptive statistics will be calculated to describe the demographics of the respondent groups per country.

We will use logistic regression analyses with acceptability of the intervention as the dependent variable to examine differences in acceptability between group and countries. ‘*Do not know*’ as a response option is often ignored and excluded from the denominator. A dichotomous variable will be create with a denominator of ‘acceptable versus not acceptable plus do not know’. The analyses will be unadjusted and adjusted for the most important life view or personality parameter (religion for euthanasia, planning for the other interventions). We will explore associations between acceptability and participant characteristics (gender, educational level, age, severity of cognitive impairment for persons with dementia, and palliative care training for physicians) and personality (locus of control, coping), depression, medical decision making, professional or personal experience with dementia, physician’s comfort with end-of-life conversations, and caregiver burden, and life view (religion, death anxiety/attitude, preparedness for end of life, priority quality vs. quantity of life, illness cognition). For this, we will use stepwise backward regression analyses. The analyses will be done with and without adjustment for country and group (forced in the stepwise regression analyses).

Qualitative data from the interviews will be used to map possible ambiguity regarding being in control through the interventions, and as to why and in what situation the participant feels the interventions are acceptable. A content analysis regarding acceptability of the interventions will be conducted. Additionally, across all interviews, we will conduct a thematic analysis on perceptions of control. Data collection and data analysis will be executed iteratively. Coding is supported by the software program ATLAS.ti.

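### The exploratory hypothesis that individual differences outweigh country and group for ACP is not answered by backward stepwise models, and ACP probably has too few events under the plan's own rule

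*Protocol article*

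**What the plan says.** Hypotheses, in the paragraph on explorative analyses, states for ACP that "individual differences may be more important than differences between countries and respondent groups". The same sentence adds that people who cope by planning should more often accept the interventions. Sample size calculation sets the status of this work: "Testing of associations with other characteristics, i.e. life view and demographic and personality characteristics, is exploratory".

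Data analyses gives two routes. Country and group differences are modelled by logistic regression, unadjusted and adjusted for one named parameter per intervention; for ACP that parameter is planning. For the wider list of characteristics, "we will use stepwise backward regression analyses", and "The analyses will be done with and without adjustment for country and group", these two being forced in when present. The outcome is acceptable against not acceptable plus don't know.

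Adjustments to protocol re-sizes the study on 300 physicians, 7 variables and 70 events. It reports that ACP has so far been accepted by nearly everyone in three countries, without a percentage. It says that the events "would not suffice for interventions that are (not) acceptable for the large majority of the respondents" and that associations matter less for such interventions. It also makes the dyad data mainly qualitative.

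**The concern.** The hypothesis asks which block explains more of the variation in ACP acceptability: individual traits, or country and group. Backward selection asks which traits survive a removal rule. Because country and group are fixed in or out, they do not go through the same process as the traits, and the article names no quantity that sets one block against the other. Traits picked from a long list on the same data also look stronger than they are, whereas country and group are not picked.

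The hypothesis is also tied to the intervention that the article itself describes as near ceiling, where its own events rule is hardest to meet. Hypotheses and Adjustments to protocol therefore pull in different directions. At stake is a possible statement, in a cross-cultural study, that personal traits matter more than country when the analysis cannot show it.

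**Working it through.** **1. The plan's own figures.** 6 × 50 = 300 physicians. 7 variables × 10 events = 70 events. Both reproduce. The full adjusted sample is 6 × (50 + 15 + 15) = 480.

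**2. Non-acceptance needed for 70 events.** Here non-acceptance means not acceptable plus don't know.
- Physicians: 70 / 300 = 23.3%.
- All respondents: 70 / 480 = 14.6%.

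**3. Events available.** Events = N × non-acceptance; terms supported = events / 10. The rates are assumptions, because the article gives none for ACP.

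| Non-acceptance | Events, N = 300 | Terms | Events, N = 480 | Terms |
|---|---|---|---|---|
| 5% | 15 | 1.5 | 24 | 2.4 |
| 10% | 30 | 3.0 | 48 | 4.8 |
| 20% | 60 | 6.0 | 96 | 9.6 |

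**4. Terms required before any trait enters.** Six countries need 5 terms. Among physicians group does not vary, so 5 is the count (50 events). Across all three groups it is 5 + 2 = 7 (70 events). At 5-10% non-acceptance neither is supported.

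**5. Candidate traits for physicians.** From Data analyses and Table 1, at one term each:
- 7 coping subscales, 2 locus-of-control scores, 1 death anxiety score, 5 death attitude items and 3 illness statements, which makes 18;
- gender, education, age, palliative training, professional experience, personal experience, comfort with end-of-life talks, religion and medical decision making, which makes 9.

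The total is 18 + 9 = 27. Coding categorical items with several terms would change it.

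**6. What selection does when nothing is related to the outcome.** Data were simulated with 300 physicians in six equal countries and 27 independent noise traits. Backward elimination removed terms at p > 0.05; the threshold is an assumption, since the article states none. A block's contribution is twice the drop in log-likelihood when that block is removed from the joint model.
- About 1.5 noise traits survive.
- Mean Nagelkerke R² is about 0.035 for surviving traits and 0.023 for country at a 50% outcome, and 0.060 and 0.033 at 10% non-acceptance.
- The survivors out-contribute country in roughly 57-69% of runs.

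With only 20 candidates, at least one noise trait survives in about 60-70% of runs. Survivors then out-contribute country in about 45-54% of physician runs, and country plus group in about 34-42% of runs with N = 480. The ordering that comes out of selection is therefore not evidence for either block.

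**The case against.** Much of the defence is fair. The hypothesis is exploratory and worded cautiously. The shortfall in events is disclosed, and the article says that associations are then of less interest. Data analyses also contains a route without selection: the models adjusted for planning, which test the one concrete trait in the hypothesis. Those models bear on planning alone, however, and not on individual differences as a block.

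The acceptance rate is also open. Don't-know answers count as non-acceptance, there are two acceptability measures, and three countries are not in the interim remark. At 20% non-acceptance among 480 there would be 96 events, enough for the 7 country and group terms with room for about two traits.

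Two stronger readings are tempting, and the documents do not support them.
- A reader might infer that the plan is bound to confirm the hypothesis. That would follow if all candidates stayed in the model, but backward elimination removes most of them, and with 20 candidates and N = 480 noise wins in fewer than half of runs. A real country effect lowers this further: with 20 noise traits, 300 physicians and a country spread of 0.5 on the log-odds scale, noise wins in 18% of runs at 10% non-acceptance and 5% at a 50% outcome.
- A reader might infer that odds ratios will be compared between runs with and without country and group. The article proposes no such comparison.

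It can also be said that the choice of fit measure belongs in a fuller plan. That is true of the measure, but the article does fix the method, and selection is the wrong method for this question.

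**Conclusion.** The point holds as a minor one. The stepwise models in Data analyses do not answer the block comparison in Hypotheses, and the planning-adjusted models answer only one part of it. After selection from noise, traits appear to outweigh country in roughly 57-69% of physician runs. This rests on 27 independent candidates and removal at p > 0.05, both assumed, and the share is lower with fewer candidates or when group is included.

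By the plan's own rule, ACP needs 23.3% non-acceptance in physicians or 14.6% overall to reach 70 events. Under the interim description this is unlikely, but it cannot be settled without a percentage. The fault in the article is an unreconciled pair of statements: an ACP-specific hypothesis about associations, and a later remark that associations matter less where nearly everyone accepts. Nothing is concealed, and the primary objective is unaffected.

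**What to change.** For this hypothesis only, replace stepwise selection with three models on one fixed analysis set: country (and group, where dyads are included) alone; a short trait block named in advance, with planning in it; and both together. Report each block's likelihood-ratio gain over the other and an optimism-corrected measure of fit.

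Let the events rule set the size of the trait block. As an illustration with three traits, physicians need (5 + 3) × 10 = 80 events, or 80 / 300 = 26.7% non-acceptance. All respondents need (7 + 3) × 10 = 100 events, or 100 / 480 = 20.8%.

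Add to Hypotheses that, where ACP acceptability is too near ceiling to meet the rule, the hypothesis is addressed descriptively only, in line with Adjustments to protocol. The stepwise runs can stay for the other exploratory associations.

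The cost is a few sentences and little computing, with no new data. The downside is that the ACP hypothesis may be openly downgraded.
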